Anlotinib is also a pan-inhibitor of VEGFR, which also inhibits *PDGFR*, *FGFR*, c-*KIT* and other targets, and would have synergistic antitumor effect in combination with the PARP inhibitor fluzoparib theoretically. However, till now no clinical study on the combination of anlotinib and fluzoparib have been reported or registered. Pharmacokinetically, anlotinib is not the substrates of P-glycoprotein, mainly metabolized via CYP1A2 and CYP3A4/5, and mostly excreted in urine and feces. In terms of drug interactions, anlotinib has a moderate inhibitory effect on CYP3A, CYP2B6, CYP2C8, CYP2C9 and CYP2C19. Grade 3 or higher adverse reactions are mainly hypertension, hand-foot skin reaction and proteinuria. Fluzoparib is a substrate of the efflux transporter P-glycoprotein mainly metabolized via CYP3A4, and is mostly excreted as metabolites in urine and feces. In terms of drug interactions, fluzoparib has a relatively small effect on the inhibition of each CYP enzyme subtype and does not induce CYP3A4 or CYP1A2. The most common grade ≥ 3 treatment-emergent adverse events reported in the fuzuloparib group were anemia (25.1%), decreased platelet count (16.8%), and decreased neutrophil count (12.6%) [12]. The above pharmacokinetic studies showed metabolic transformation is the main pathway of anlotinib elimination, while renal excretion via urine was the main excretion route and fecal excretion was the secondary excretion route of fuzuloparib, therefore, the toxicity of the two drugs should not add up theoretically. In addition, real-world study data for a small number of patients treated with fluzoparib in combination with anrotinib showed no significant increase in toxic and side effects.

The combination of anlotinib and fluzoparib may theoretically decrease the metabolism of fluzoparib, increase its concentration in the blood and area in the drug curve. Therefore, fluzoparib dose should be reduced appropriately. Combination of anlotinib and fluzoparib would not make adverse events and not increase the incidence of ≥ grade 3 adverse events. In theory, it is feasible in combination of the anlotinib and fluzoparib.

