6	Have received chemotherapy, radiotherapy or other experimental anticancer therapy (other than bisphosphonates) within 4 weeks prior to the first dose: those who have received prior local radiotherapy may be enrolled if the following conditions are met: the radiotherapy ended more than 4 weeks (more than 2 weeks for brain radiotherapy) from the start of study treatment; and the target lesion selected for this study is not in the radiotherapy area; or the target lesion is in the radiotherapy area but has been confirmed progression.
7	Patients who have not recovered from antineoplastic therapy-related adverse effects (except alopecia) to NCI-CTCAE ≤ grade 1 after prior systemic antineoplastic therapy.
8	Abnormal coagulation (INR > 1.5 or prothrombin time (PT) > ULN + 4 s or APTT > 1.5 ULN), with prone to bleeding or on thrombolytic or anticoagulant therapy; Note: The use of low-dose heparin for prophylactic purposes (adult daily dose of 0.6 to 1.2 10,000 U) or low-dose aspirin (dosage ≤ 100 mg daily) is accepted for prophylactic purposes.
9	Clinically significant hemoptysis (hemoptysis > ½ tablespoon per day) within 3 months prior to enrollment; or clinically significant hemorrhage symptom or prone to bleeding within 4 weeks prior to cohort, such as alimentary tract hemorrhage, hemorrhagic gastric ulcer (including gastrointestinal perforation and/or fistula, but the gastrointestinal perforation or fistula that has been surgically removed may be allowed), fecal occult blood (≥ + +) at baseline, unhealed wounds, ulcers, or fractures.
10	Renal insufficiency: urine protein ≥ + + , or 24-h urine protein amount > 1.0 g.
11	Patients with poor blood pressure control (systolic blood pressure ≥ 160 mmHg and diastolic blood pressure ≥ 100 mmHg) after drug therapy.
12	Patients with severe cardiovascular disease: grade II or higher myocardial ischemia or myocardial infarction, poorly controlled arrhythmias; grade III-IV cardiac insufficiency by NYHA criteria, or cardiac ultrasound suggestive of left ventricular ejection fraction (LVEF) < 50%.
13	The current presence of peripheral neuropathy ≥ CTCAE degree 2, except the cause of trauma.

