14	Moderate or large uncontrolled plasma cavity effusions (including pleural, ascites, and pericardial effusions) via fluid aspiration, exacerbated chronic obstructive pulmonary disease, and respiratory disease in the active phase of pulmonary infection and/or acute bacterial or fungal infection that should accept intravenous antibiotic therapy.
15	There are factors that significantly affect absorption of oral drugs, such as inability to swallow, chronic diarrhea and intestinal obstruction.
16	Arterial/venous thrombotic events such as cerebrovascular accidents (including cerebral hemorrhage and cerebral infarction), deep vein thrombosis and pulmonary embolism that occurred within the 6 months prior to cohort.
17	Known history of psychotropic substance abuse, alcohol or drug abuse.
18	Active hepatitis (hepatitis B: HBsAg positive and HBV DNA ≥ 1 × 104 copies/ml; hepatitis C: HCV RNA positive and abnormal liver function) that cannot be controlled, or the combined infection of hepatitis B and C.
19	The positive blood or urine pregnancy result of women within 3 days prior to the first dose.
20	Poor compliance in the procedures and requirements of the study.
21	Any condition that will endanger patient's life or interference assessment results.

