**Anlotinib**			
**Abnormal liver function**	**Grade 1**	**Conduct follow-up as planned**	**8 mg****, ****qd**
	**Grade 2 (normal baseline)**	**Delay dose, strengthen guarantees the liver treatment and close monitoring of liver function once a week till < grade 2 within 2 weeks, and then continue anlotinib at a lower dose level**	**8 mg****, ****qod**
	**Grade 2 (abnormal baseline)**	**Strengthen guarantees the liver treatment and close monitoring of liver function once a week, continue anlotinib at an o initial dose**	**8 mg****, ****qd**
	**Grade 3**	**Delay dose, strengthen guarantees the liver treatment and close monitoring of liver function twice a week till < grade 2 within 2 weeks, till < grade 2 within 2 weeks, and then continue anlotinib at a lower dose level**	**8 mg****, ****qod**
	**Grade 4**	**Strengthen guarantees the liver treatment and close monitoring of liver function once/twice a week till < grade 2. Or have reasons for this issue**	**Discontinue anlotinib**
**Hypertension**	**SBP 120–139 mmHg or DBP 80–89 mmHg**	**Closely monitor, continue anlotinib at an initial dose**	**8 mg****, ****qd**
	**Asymptomatic grade 2 hypertension**	**Continue anlotinib at an initial dose. Start taking antihypertension medication or adjust its dose till blood pressure is effectively controlled (SBP < 140 mmHg or DBP < 90 mmHg) within two weeks, otherwise dose can be reduced as per investigator’s discretion**	**8 mg****, ****qd, or dose can be reduced as per investigator’s discretion**
	**Symptomatic grade 2 hypertension, or grade 3 hypertension**	**Discontinue anlotinib, and then start taking antihypertension medication or adjust its dose till blood pressure is effectively controlled within two weeks, continued anlotinib at an initial dose or a lower dose level**	**8 mg****, ****qd, or 8 mg****, ****qod as per investigator’s discretion**
**Abnormalities of bleeding and coagulation**	**Grade 1**	**Closely monitor, continue anlotinib at an initial dose**	**8 mg****, ****qd**
	**Grade 2**	**Discontinue anlotinib, till AE ≤ 1, and then continue anlotinib at a lower dose**	**8 mg****, ****qod**
	** ≥ Grade 3, or ≥ Grade 2 occurred twice (after discontinue or dose adjustment)**		**Withdraw from the pilot study**

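### Exclusion 11 needs both blood pressure limits to be breached, so a treated patient with one high value is not excluded by it, and its and/or logic is not reconciled with Table 2

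*Protocol article*

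**What the plan says.** Four places in the protocol article bear on this.

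- **Eligibility criteria, Table 1, exclusion 11:** "Patients with poor blood pressure control (systolic blood pressure ≥ 160 mmHg and diastolic blood pressure ≥ 100 mmHg) after drug therapy". It is the only numeric blood pressure criterion in the table. Exclusion 12 deals with ischaemia, arrhythmia, cardiac insufficiency and ejection fraction. Exclusion 21 is a general catch-all: "Any condition that will endanger patient's life or interference assessment results".
- **Intervention, Table 2, anlotinib, hypertension:** the lowest band is "SBP 120–139 mmHg or DBP 80–89 mmHg". The row that stops the drug applies to "Symptomatic grade 2 hypertension, or grade 3 hypertension", with the action "Discontinue anlotinib, and then start taking antihypertension medication or adjust its dose till blood pressure is effectively controlled within two weeks"; anlotinib may then resume at the initial or a lower level. Table 2 names CTCAE 5.0 as its scale but prints no mmHg limits for grade 2 or grade 3.
- **The same table, asymptomatic grade 2 row:** treatment is adjusted until "blood pressure is effectively controlled (SBP < 140 mmHg or DBP < 90 mmHg) within two weeks".
- **Background:** on anlotinib, "Grade 3 or higher adverse reactions are mainly hypertension, hand-foot skin reaction and proteinuria".

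**The concern.** A site that applies exclusion 11 as printed turns away only patients who are high on both components. Nothing in Table 1 suggests a looser reading. Where either limit is enough, the table says *or* (the coagulation tests in exclusion 8, the two urine protein measures in exclusion 10). Where both are meant, it says *and* (hepatitis B antigen with viral load in exclusion 18).

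Hypertension is the first reaction the Background names among the main severe ones for anlotinib. The Endpoints section counts adverse events, and the proportions of patients with dose adjustment or withdrawal because of them, as safety endpoints. With no control arm, hypertension already present at entry is hard to tell apart from hypertension caused by treatment. If entry and on-treatment rules follow different logic, some patients may also have anlotinib interrupted for a condition they brought with them.

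**Working it through.** The plan gives no figure to reproduce. The check is one of logic, followed by an illustration of size.

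**Step 1. The printed rules as logical statements (S = systolic, D = diastolic, mmHg)**

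- Exclusion 11 applies if S ≥ 160 *and* D ≥ 100. A patient therefore passes it if S < 160 *or* D < 100.
- Table 2 control is met if S < 140 *or* D < 90.
- Table 2 lowest band is met if S is 120–139 *or* D is 80–89.
- Table 2 interruption row: symptomatic grade 2, or grade 3; no mmHg limits printed.

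**Step 2. Example readings on treatment**

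| Reading | Excluded as written (*and*) | Excluded if *or* were meant | Controlled under Table 2, literal *or* | Controlled if both values must be low |
|---|---|---|---|---|
| 165/105 | yes | yes | no | no |
| 180/90 | no | yes | no | no |
| 150/106 | no | yes | no | no |
| 200/85 | no | yes | yes | no |
| 155/95 | no | no | no | no |

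The readings 180/90 and 150/106 pass exclusion 11, yet fail Table 2's control definition on either reading of its *or*. The reading 200/85 passes exclusion 11 and, taken literally, counts both as controlled and as inside Table 2's lowest band, because D = 85 alone satisfies each.

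**Step 3. Does such a patient enter already in the interruption row?**

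This depends on a grade 3 limit that the article does not print. For 180/90:

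- if grade 3 means S ≥ 160 or D ≥ 100 (assumption), the row is met, with or without symptoms;
- if grade 3 needs both values, or a systolic value above 180, an asymptomatic patient is not in the row;
- if the patient has symptoms and is at least grade 2, the row is met either way.

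**Step 4. Illustration of size**

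The article gives no blood pressure distribution. Assume bivariate normal values in two scenarios, with correlation 0.5 to 0.7. Then P(either) = P(S ≥ 160) + P(D ≥ 100) − P(both), and P(exactly one) = P(either) − P(both).

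- Scenario A, mean 135/80, SD 18/11: z = (160 − 135)/18 = 1.389, so P = 0.0824; z = (100 − 80)/11 = 1.818, so P = 0.0345.
- Scenario B, mean 130/78, SD 16/10: z = (160 − 130)/16 = 1.875, so P = 0.0304; z = (100 − 78)/10 = 2.2, so P = 0.0139.

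| Scenario | Correlation | Both | Either | Exactly one | Exactly one, per 50 | Both ÷ either |
|---|---|---|---|---|---|---|
| A | 0.5 | 1.3% | 10.4% | 9.1% | 4.6 | 12% |
| A | 0.7 | 2.0% | 9.7% | 7.7% | 3.8 | 21% |
| B | 0.5 | 0.3% | 4.1% | 3.7% | 1.9 | 8% |
| B | 0.7 | 0.6% | 3.8% | 3.2% | 1.6 | 16% |

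Worked example (A, 0.5): 0.0824 + 0.0345 − 0.0129 = 0.1040, and 0.1040 − 0.0129 = 0.0911. Percentages come from unrounded values. The group that passes exclusion 11 with one high value is about 3% to 9% of candidates, or roughly 2 to 5 per 50.

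**The case against.** The strongest reply has four parts.

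1. **The interruption row rests on an unprinted limit.** A reader might infer that a patient passing exclusion 11 with one high value is already in that row on day 1. Table 2 gives no mmHg value for grade 3, so for an asymptomatic patient this holds only under an assumption. This stands, and the claim is made only conditionally here.
2. **The entry and on-treatment rules are not simply opposites.** A reader might infer that Table 2 uses the same limits with reversed logic. The figures 160 and 100 do not appear in Table 2, and its control definition has the same form as passing exclusion 11: one low value is enough. This also stands. The tension is with the either-component lowest band and possibly the graded rows. Changing one word in exclusion 11 alone would leave it at odds with the control definition.
3. **Exclusion 21 can keep out a severe case.** True, so such a patient is not necessarily eligible. But a discretionary clause does not repair a specific numeric rule, and sites may apply it differently.
4. **The consequences are limited.** Table 2 lets anlotinib resume once pressure is controlled, so an interruption delays exposure and need not remove it. No effect on the response rate can be derived from the article, and the size in the illustration rests on assumed distributions that are not tied to treated patients. All of this is correct.

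What remains is a stated eligibility rule that, followed exactly, passes marked elevation of one component, and a control definition with a matching fault.

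**Conclusion.** The point holds in a limited form. By its own wording, exclusion 11 does not exclude a treated patient with only one value at or above its limit. That conclusion needs no outside source. Nor does the finding that Table 2's control definition, read literally, accepts 200/85.

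Whether such a patient starts treatment already in the row that stops anlotinib is conditional on the grade 3 limit, as set out in the working. The documents do not support saying that the patient is certainly eligible or certainly in that row, and they do not settle which connective or limit is clinically right.

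The affected share is unknown. About 3% to 9% of candidates is an illustration under assumed distributions, not an estimate for this trial. The sample size and the test of the primary endpoint are untouched. What is exposed is the consistency of enrolment across sites and the interpretation of the hypertension and dose-adjustment figures in a single-arm study. It should be corrected, mainly because the correction is cheap.

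**What to change.** - **Wording.** Reconcile exclusion 11, Table 2's control definition and its graded hypertension rows so that all state explicitly whether one or both components decide, under one consistent logic. State in Table 2 the mmHg limits meant by grades 2 and 3, so that a reading falls in one row only. The limits and the choice of logic are clinical decisions for the sponsor.
- **Patients already enrolled.** Flag those whose baseline systolic or diastolic value is at or above the limits printed in exclusion 11. Report hypertension as change from baseline grade, and show hypertension-related dose adjustments and withdrawals with and without the flagged patients, so that pre-existing hypertension is not counted as a drug effect.

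The cost is a short amendment to two tables, one derived baseline variable and one extra line in the safety tables. If the sponsor's reconciled rule is stricter than the present one, a few candidates may enter later or not at all.

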**Withdrawal from the study criteria**	
1	Withdrawal of informed consent form at any time by the subjects
2	Disease progressed assessed by medical imaging or clinical feature.
3	A pregnancy event occurs in the subject during the study
4	Other reasons that the trial treatment cannot be continued by the investigator The subject have to discontinue drug upon the occurrence of any of the following (including but not limited to)

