### Intervention

Eligible patients will receive oral fluzopalib150mg twice daily and oral anlotinib 8 mg once daily until disease progression or development of intolerable toxic side effects. The dose giving and dose level adjustment are shown in Table 2.

**Table 2 Tab2:** Dose adjustment criteria

NCI CTCAE 5.0		Management (after active treatment and observation)	Dose adjustment after the study drug is continued

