### Endpoints

The primary endpoint is Objective Response Rate. The secondary endpoints are progression-free survival, disease control rate, safety, duration of response, overall survival, quality of life. The safety endpoints are occurrence of adverse events, proportion of patients withdrawn due to adverse events, proportion of patients with dose adjustment due to adverse events. We will closely evaluate and monitor safety information in accordance with safety information evaluation and management practices during drug clinical trials. We will timely submit suspected and unexpected serious adverse reactions (SUSAR) reports through the pharmacovigilatory Electronic Transmission System (PV system), and timely submit safety update reports (DSUR) during the study and other potential serious safety risk information reports through the Drug Approval Center website. We will carry out risk monitoring, identification, assessment and control of safety information, timely discover existing safety problems or other risks, and promptly take measures of risk control and risk minimization, including general risk management measures (such as modifying clinical trial protocol), active suspension or termination of clinical trials.

Efficacy evaluation will be performed every two cycles (i.e., every 6 weeks) from 24 weeks after the first dose. All imaging data will be kept for patients with CR, PR, SD, and PD. If subjects discontinue the trial before the development of PD, follow up every 6 weeks for imaging (external hospital reports are acceptable) to observe whether the tumor progresses or take other anti-tumor therapies. Telephone or clinical follow-ups are acceptable.

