### Statistical analysis

The sample size consideration was based on the unilateral exact test with α = 0.05 (unilateral), β = 0.20, and the second-line standard treatment plan recommended by the current guidelines for topotecan single-agent treatment of refractory SCLC patients with ORR of 9.4% [4]. There is 80% power to detect a significant difference of 9.4% in ORR (from 30%) between treatments based on a one-sided 5% significance level, 22 evaluable subjects need to be enrolled at least. Considering a dropout rate of 10%, a total of 25 subjects are expected to be enrolled. All things considered, 50 subjects are planned to be enrolled in this study. Median PFS and OS were estimated using Kaplan–Meier method. The two-sided statistical test is performed for statistical analysis.

Means, standard deviations, medians, maxima, and minima are listed for measurement data, and frequencies (composition ratio), rates, and confidence intervals are listed for count data and rank data. Statistical analyses were carried out with statistical software package SPSS 24.0. *P* less than 0.05 was considered as statistically significant. No data imputation will be performed for the missing data.

The mean, standard deviation, median, maximum and minimum values of quantitative data, such as age, height and weight are calculated for basic patient characteristics. The frequencies and percentages are listed for qualitative data, such as gender and ECOG scores.

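### Progression is listed as a reason to leave the study and off-trial follow-up covers only patients without progression, which conflicts with overall survival as an endpoint

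*Protocol article*

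**What the plan says.** - **Table 1, withdrawal block.** Under the heading "Withdrawal from the study criteria", item 2 reads "Disease progressed assessed by medical imaging or clinical feature". It stands in the same list as withdrawal of consent. Item 4 of that list uses treatment language instead: "Other reasons that the trial treatment cannot be continued by the investigator".
- **Intervention.** Both drugs are given "until disease progression or development of intolerable toxic side effects", so progression also ends treatment.
- **Table 2, anlotinib.** Stopping anlotinib and leaving the study are worded differently here. The most severe liver category stops the drug, while the most severe bleeding category says "Withdraw from the pilot study".
- **Endpoints, off-trial follow-up.** "If subjects discontinue the trial before the development of PD, follow up every 6 weeks for imaging". The stated purpose is to detect progression or a new anticancer therapy. Vital status is not named. Contact by telephone or in clinic is accepted.
- **Endpoints, list.** "The secondary endpoints are progression-free survival, disease control rate, safety, duration of response, overall survival, quality of life".
- **Statistical analysis.** "Median PFS and OS were estimated using Kaplan"-Meier methods. No censoring rule for OS is printed.

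**The concern.** Three printed statements do not fit together: progression takes a patient out of the study, continued follow-up is described only for patients who leave before progression, and OS is to be estimated for the trial.

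If the first two were followed literally, survival time after progression would not be recorded. A Kaplan-Meier analysis would then have to censor those patients at progression. That censoring is informative, because a patient who has just progressed is more likely to die soon than one who has not. Only deaths without prior progression would count as events, and the curve would sit too high.

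The trial has a single arm, so its OS can only be read against outside figures such as those in the Discussion. No concurrent control would carry the same bias and reveal it.

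**Working it through.** **The plan's own figure.** The article gives no target or expected value for OS. Its only design calculation is for objective response rate, and it reproduces. Reading 30% as the target rate and 9.4% as the null, an exact one-sided test with 22 patients and at least 5 responses has α = 0.0498 and power 0.835, and 22/0.9 = 24.4, rounded up to 25. OS does not enter this calculation.

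**Inputs for the illustration**
- Median PFS 4.1 and median OS 7.3 months: the placebo-controlled anlotinib trial in small cell lung cancer (Discussion).
- Median PFS 4.2 and median OS 8.5 months: the olaparib plus temozolomide study (Background).
- d, the share of first PFS events that are deaths: assumed, 5% to 40%.
- Exponential times, with d constant over time: assumed.

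**Formula.** Let m be the median PFS. The hazard of a first PFS event is ln 2 / m, of which d × ln 2 / m is death without prior progression. If every progression is censored, Kaplan-Meier estimates exp(−d × ln 2 × t / m), whose median is m/d.

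| d | apparent median, m = 4.1 | ratio to 7.3 | apparent median, m = 4.2 | ratio to 8.5 |
|---|---|---|---|---|
| 5% | 82 | 11.2 | 84 | 9.9 |
| 10% | 41 | 5.6 | 42 | 4.9 |
| 20% | 20.5 | 2.8 | 21 | 2.5 |
| 30% | 13.7 | 1.9 | 14 | 1.6 |
| 40% | 10.2 | 1.4 | 10.5 | 1.2 |

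**Direction.** The apparent median exceeds the reference whenever d is below 4.1/7.3 = 56%, or 4.2/8.5 = 49%. The bias is therefore upward over the whole assumed range.

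**Why.** With post-progression survival calibrated so that true median OS is 7.3 months, its median is 2.65 months at d = 20%. The death hazard after progression is then (4.1/0.2)/2.65 = 7.7 times that before it. At d = 40% the post-progression median is 3.91 months and the ratio is 10.25/3.91 = 2.6.

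**Twelve-month OS at d = 20%, m = 4.1.** The apparent value is 0.5^(12 × 0.2/4.1) = 67%. The calibrated true value is 26%, and the cited trial reports 30.6%.

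**Would 50 patients show a median?** If all 50 reached a first PFS event, the deaths counted would be 50 × d: 5 at 10%, 10 at 20%, 20 at 40%. A simulation with 50 patients and an assumed uniform 12 to 24 months of follow-up found that the apparent median is reached in about 11% of trials at d = 10%, 35–39% at 20%, 73–75% at 30% and 94–95% at 40%. The first symptom of the bias would often be a median reported as not reached.

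**The case against.** The strongest objection is that the list was probably meant as criteria for stopping treatment. Item 4 speaks of treatment that cannot continue and of stopping the drug, item 2 matches the treatment duration under Intervention, and the list breaks off after item 4 in the text at hand. The follow-up sentence under Endpoints concerns imaging, and it is normal to stop scans after progression without stopping survival contact. A journal article may also leave survival calls and censoring rules to the full protocol or analysis plan.

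Much of this stands. A reader might infer that OS will be censored at progression. The documents do not support that: no censoring rule is printed, and the wording allows the treatment-stop reading. The objection does not remove the conflict. The heading names the study, the list includes consent withdrawal, and the article words stopping a drug and leaving the study differently elsewhere. The point rests on a printed rule that contradicts an endpoint, not on a missing detail.

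Two further inferences fail:
- A reader might conclude that patients withdrawn for bleeding drop out of PFS. They have left before progression, and the Endpoints section continues their imaging every 6 weeks. Nor does the article say that patients with clinical progression are censored for PFS; Table 1 describes them as progressed.
- A reader might take an apparent median of 20 to 41 months as the expected result. That range needs d of 10% to 20%. At 40% the overstatement is only 1.2- to 1.4-fold, and at 20% or below the median would usually not be reached. The anlotinib trial also enrolled patients with at least two prior regimens, whereas this is a second-line study, so it serves only to set a scale.

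**Conclusion.** The concern holds as an internal conflict. Table 1 withdraws patients from the study at progression, the Endpoints section follows only those who leave before it, and OS is still to be estimated. If the text is followed literally, survival after progression is not observed and OS is not validly estimable. Censored at progression, its median would be overstated by about 1.2- to 1.4-fold if 40% of first PFS events are deaths, 2.5- to 2.8-fold at 20%, and 5- to 6-fold at 10%. These sizes rest on exponential times, medians borrowed from cited studies and an assumed d; only the upward direction is common to the whole range.

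Severity is moderate. OS is one of several secondary endpoints, and the objective response rate and its sample size are unaffected.

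**What to change.** Reconcile the withdrawal block of Table 1 and the follow-up paragraph under Endpoints with the OS endpoint:

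1. Split the block into two lists, one for stopping study treatment and one for leaving the study, so that a patient who stops treatment is not thereby lost to follow-up. This changes no treatment rule.
2. State that vital status is followed after progression until death, withdrawal of consent to follow-up, or data cut-off, using the telephone contact that the Endpoints section already accepts.

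No additional scan is needed. The cost is a wording change and a small number of survival calls among at most 50 planned patients. If the full protocol already provides for this follow-up, only the wording needs correcting. If patients have in fact been released at progression, survival data not collected may not be recoverable, and OS should then be reported as not validly estimable.
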